### Acute Care for Elders Program: Best Practice Guidelines for Elder Care Transitions

Improving care transitions for seniors requires a multifaceted integrated approach based upon best practices [11,38], such as the Acute Care for Elders (ACE) program developed by Mount Sinai Hospital in Toronto [39-41]. Over the last decade, Mount Sinai has become Canada’s most widely recognized elder-friendly hospital, implementing evidence-informed point-of-care interventions to improve patient, provider, and system outcomes for frail older persons [2]. Supported by systematic reviews [42-48] and randomized clinical trials [49-52], the ACE care transition program is based on interprofessional interventions to enhance postdischarge care. Comparing performance in the baseline year 2009 with that in 2014, Mount Sinai reduced the total length of stay (from 12 to 8 days), reduced the alternate level of care days by 20%, reduced readmissions within 30 days (from 15% to 13%), improved the rate of patients returning home as opposed to other institutional settings (from 71% to 79%), and increased the rate of patient satisfaction (from 95% to 97%). These improvements resulted in an estimated Can $4.2 million (US $2.6 million) in savings in 2014 [53].

Unfortunately, the ACE best practice guidelines have only been implemented in a few dozen acute care organizations around the world [54]. A major barrier to their implementation is that these guidelines and tools cannot be easily transferred into different cultural, organizational, and technical contexts. Knowledge producers (researchers) and knowledge users (patients/caregivers, clinicians, and decision makers) lack effective interventions to adapt knowledge to the local context, a crucial step in the knowledge-to-action (KTA) framework [55,56]. Knowledge users lack the skills, resources, or institutional culture necessary to apply knowledge locally and support their institutions to learn new ways of operating. Researchers have been challenged to find new solutions that support the involvement of local knowledge users in adapting knowledge tools to their contexts [57-61]. Although local adaptation is a key step of the KTA framework, little is known about how to accomplish this step effectively [55,56,62,63]. New solutions are needed to support the involvement of knowledge users in adapting knowledge tools to their contexts [56-60].

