## Methods

### Study Design

Our study will have two main parts (Figure 1). Part 1 will involve the staggered implementation of the context-adapted CISSS-CA ACE program across four CISSS-CA sites (Hôtel-Dieu de Lévis, St-Georges, Montmagny, and Thetford Mines). We will use an interrupted time series (ITS) to measure the impact of the CISSS-CA ACE program and its context-adapted tools on all hospital-level outcomes (Table 1 and Figure 2). This design will allow us to better measure the effect of our intervention on our outcomes while controlling for secular trends in our data by comparing retrospective monthly data collected in the CISSS-CA administrative databases for 36 months before our intervention and for a maximum of 12 months after our intervention in the last targeted CISSS-CA implementation site (Hospital 4 is yet to be determined) and for up to 21 months in the first targeted CISSS-CA implementation site (Hospital 1 is the Hôtel-Dieu de Lévis). Part 2 will be a parallel mixed-methods process evaluation study to understand the underlying human, organizational, and technical factors that influence the success or failure of our intervention and, more specifically, of our Wiki-suite to facilitate it through the adaptation and uptake of geriatric knowledge tools. We will report this implementation study using the Standards for Reporting Implementation Studies (StaRI) reporting guidelines (Multimedia Appendix 1) [71]. This study has been approved by the CISSS-CA Ethics Review Committee (project #2018-462, 2018-007).

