#### Sample Size and Statistical Analysis

We will use segmented regression statistics to measure the changes in the level and slope in the postintervention period compared with the preintervention period in each center for each of our primary and secondary outcomes [92]. Thus, we will present a regression model with different intercept and slope coefficients for the pre- and postintervention time periods for each center. We will compare the changes in a composite primary outcome (total 30-day hospital readmission and ED visit rate) at our four intervention centers. We will use a Durbin-Watson test to verify the presence of autocorrelation and use an autoregressive error model to correct for this serial correlation. For an ITS, 10 measurement points before and 10 points after an intervention provide 80% power to detect a change in the level of 5 standard deviations (of the predata) only if the autocorrelation is greater than 0.4 (ie, extent to which data collected close together in time are correlated with each other) [93].

We have calculated the sample size for our patient cohort, which will be based on the smallest clinically significant difference (ie, 11%) that the CTM-3 can capture on a maximum score of 100. To detect a difference of 11% with a type I error of 5% and a type II error of 20%, 38 patients per month are needed to calculate a monthly CTM-3 estimate, based on a previous study in which CTM-3 was measured in 21 patients at Hôtel-Dieu Hospital in Lévis and showed an average of 75% and a standard deviation of 23%. Considering a call rejection rate of 70%, the number of people to be contacted in total will be 127 patients per month for each ED. We will therefore contact 5 patients per day in each of the four participating centers to obtain our targeted sample size of 38 patients at the end of the month. To ensure the creation of a random and representative sample of our population of elderly patients being discharged from the ED, a randomization table based on all patients discharged in the previous 24 hours from the ED will be provided every day to select which patients to call.

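### The only power statement for the primary interrupted time series describes a different series from the one planned and does not hold for the protocol's own regression model

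*Protocol article*

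**What the plan says.** Sample Size and Statistical Analysis sets out the model and the power statement in the same paragraph.

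- **Model:** "We will use segmented regression statistics to measure the changes in the level and slope in the postintervention period", presented as "a regression model with different intercept and slope coefficients for the pre- and postintervention time periods for each center". Autocorrelation is to be tested with Durbin-Watson and corrected with an autoregressive error model.
- **Power:** "10 measurement points before and 10 points after an intervention provide 80% power to detect a change in the level of 5 standard deviations", with the condition "only if the autocorrelation is greater than 0.4". The SD is that of the pre-intervention data. The sentence carries a literature citation.
- **Planned series** (Study Design): monthly administrative data "for 36 months before our intervention and for a maximum of 12 months after our intervention" at the last hospital, and up to 21 months after at the first.

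The article gives no alpha, autoregressive order, expected autocorrelation, monthly SD or target effect for the primary composite. Its only other calculation, 38 patients per month, is for the CTM-3, a secondary outcome.

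**The concern.** Two things look wrong. The statement is for "10 measurement points before and 10 points after an intervention", while the plan has 36 before and 12 to 21 after. And a 5-SD level shift is so large against month-to-month noise that 80% power from 20 points looks far too low. It is also odd that power should depend on autocorrelation being high, when the same paragraph treats autocorrelation as something to test for and correct.

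At stake is what the article tells readers about the sensitivity of its primary analysis. As printed, it gives no figure that applies to the planned series, and the figure it does give is much too pessimistic even for 10+10 points.

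**Working it through.** **Inputs from the protocol.** 10+10 points, 5 SD, 80% power, autocorrelation above 0.4 (Sample Size and Statistical Analysis); 36 points before and 12 or 21 after (Study Design); separate intercepts and slopes with autoregressive errors (Sample Size and Statistical Analysis).

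**Assumed, because not stated for the time series.** AR(1) errors and a two-sided 5% test. SD is taken first as the marginal SD of the monthly series about its trend, then as the innovation SD. Post-intervention time is coded from 0, and autocorrelation is treated as known unless noted.

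**Formulae.** For month t, with D = 1 after the intervention and n1 points before it:

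y(t) = b0 + b1·t + b2·D + b3·D·(t − n1) + e(t), with e(t) = ρ·e(t−1) + u(t).

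The SE of the level change b2 is the square root of its diagonal element of (X′V⁻¹X)⁻¹, with V(i,j) = ρ^|i−j| for unit marginal SD, or that divided by (1 − ρ²) for unit innovation SD. Power is the probability that a noncentral t with n − 4 df and noncentrality δ/SE exceeds the critical value.

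**Step 1: the plan's own figure (10+10 points, 16 df, δ = 5 SD).** At ρ = 0 the noncentrality is 5/0.901 = 5.55, against a critical value of 2.12.

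| ρ | SE, marginal SD | Power | Change detectable with 80% power | Power, innovation SD |
|---|---|---|---|---|
| 0 | 0.901 | 99.9% | 2.69 SD | 99.9% |
| 0.2 | 0.985 | 99.7% | 2.94 SD | 99.7% |
| 0.4 | 1.001 | 99.7% | 2.99 SD | 99.0% |
| 0.6 | 0.910 | 99.9% | 2.72 SD | 98.5% |
| 0.8 | 0.675 | 100% | 2.01 SD | 98.6% |

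The stated 80% does not reproduce. It is already well exceeded at ρ = 0, and nothing changes at 0.4.

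**Step 2: can another reading produce the stated condition?**

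- SD as the expected sample SD of the pre-intervention data: 99.2-99.9%.
- Stricter alpha: at least 91% at 1%, and at least 87% at 0.05/8.
- Common slope before and after: at least 98.6% at two-sided 5%.
- Autocorrelation estimated (simulated Prais-Winsten): 97-100%. With critical values adjusted to restore the 5% level: 97-100% for marginal SD and 83-100% for innovation SD, the latter falling as ρ rises.
- Ordinary least squares with its true AR(1) variance and innovation SD: 80.5% at ρ = 0.8, with power falling as ρ rises.
- Level change read as the difference of intercepts at time 0 (marginal SD): 71% at ρ = 0 and 49% at ρ = 0.4.

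The last two come near or below 80%, but power there falls as autocorrelation rises from 0, the reverse of the stated condition. No variant gives 80% only above 0.4.

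**Step 3: the planned series.** Level change detectable with 80% power per site, marginal SD:

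| ρ | 36+12 (44 df): SE | Detectable | 36+21 (53 df): SE | Detectable |
|---|---|---|---|---|
| 0 | 0.641 | 1.84 SD | 0.542 | 1.55 SD |
| 0.2 | 0.732 | 2.10 SD | 0.632 | 1.80 SD |
| 0.4 | 0.796 | 2.28 SD | 0.712 | 2.03 SD |
| 0.6 | 0.784 | 2.24 SD | 0.738 | 2.11 SD |

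Sensitivity: with innovation SD at ρ = 0.6 the figures are 2.81 SD (36+12) and 2.63 SD (36+21). Coding post-intervention time from 1 gives 2.00-2.46 SD for 36+12. Estimating the autocorrelation raises them somewhat, to roughly 2.6 SD for 36+12 at ρ = 0.6 (marginal SD). Power for a 1-SD change over ρ = 0 to 0.6 is 23-33% (36+12) and 26-44% (36+21).

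**The case against.** The sentence is framed as a general rule for interrupted time series and attributed to a cited source, whose model, test, alpha and SD definition are not shown. A reader might infer that the authors miscopied it or that the source is wrong; the documents support neither. What stands is narrower: the rule does not hold for the model this protocol specifies.

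Nor does the sentence settle any design choice. Administrative data fix the series length, the planned series exceeds 10 points on both sides, and a null result can still be read from its confidence interval. That limits the consequence but does not make the figure right.

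A fuller power calculation may exist in documents not shown, and its absence here is not the complaint. The complaint is about a figure that the article prints.

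Two stronger readings should be resisted.

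- A reader might infer that the trial can detect only 5-SD shifts. Neither the text nor the calculation says so; the planned series does considerably better.
- A reader might set 5 SD against the fall in 30-day readmission from 15% to 13% quoted in the Introduction and conclude that the trial cannot see its target. That is another hospital's result for readmission alone. The primary outcome here is a composite with ED visits, no target effect is stated for it, and no monthly SD or volume is given to convert 5 SD into percentage points.

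**Conclusion.** The point holds in limited form. The mismatch between 10+10 and 36+12 to 36+21 points needs no assumption. That the statement is wrong for the protocol's own model rests on AR(1) errors and a two-sided 5% test. Under these, power for 5 SD is about 98-100% at autocorrelation 0 to 0.8 under either SD definition. The 0.4 threshold appears in no variant tried.

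The printed statement therefore understates what even 10+10 points could detect and says nothing about the planned series. The size of the correction is from 5 SD to about 1.8-2.3 SD (36+12) and 1.6-2.1 SD (36+21), for marginal SD and known autocorrelation of 0 to 0.6. Those figures move with the SD definition, the time coding and estimation of the autocorrelation, so all must be stated alongside them. Whether the detectable change is clinically useful cannot be judged from the documents.

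**What to change.** Delete the 10+10 sentence. In its place state, for each site, the level change detectable with 80% power for 36+12 and 36+21 points, giving alpha, autoregressive order, SD definition, coding of post-intervention time and the range of autocorrelation considered. For example: with AR(1) errors, two-sided 5%, marginal SD, known lag-1 autocorrelation of 0 to 0.6 and post-intervention time coded from 0, the detectable level change is about 1.8-2.3 SD with 12 months after and 1.6-2.1 SD with 21 months after. Add that at autocorrelation 0.6 it is about 2.8 and 2.6 SD if SD means innovation SD, and that it is somewhat larger when the autocorrelation is estimated.

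Then convert to percentage points using the SD of the composite from the 36-month retrospective series. The plan describes centre-specific models, so per-site figures are what is needed.

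The cost is a change of wording and one calculation on administrative data that the plan already calls for. Recruitment, data collection and the analysis model are unaffected.

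### The daily randomization table makes the list of patients called random, but with 70% expected call rejection it cannot make the phone sample representative

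*Protocol article*

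**What the plan says.** All of the following is in the protocol article.

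- **Sample Size and Statistical Analysis, the claim.** The stated purpose of the sampling scheme is "To ensure the creation of a random and representative sample of our population of elderly patients being discharged from the ED". The means offered is "a randomization table based on all patients discharged in the previous 24 hours from the ED", from which staff draw each day's calls.
- **Same paragraph, the expected yield.** "Considering a call rejection rate of 70%, the number of people to be contacted in total will be 127 patients per month for each ED". This becomes a daily workload: "We will therefore contact 5 patients per day in each of the four participating centers".
- **Same paragraph, the yardstick.** The monthly target of 38 is based on "the smallest clinically significant difference (ie, 11%) that the CTM-3 can capture on a maximum score of 100", with a standard deviation of 23.
- **Same section, the analysis.** Segmented regression for level and slope changes is planned per center for the primary and all secondary outcomes.
- **Patient and Caregiver Recruitment.** Recruitment is called consecutive in one paragraph and randomly selected in the next. A patient who declines research contact or participation keeps their CTM-3 answers out of the study.
- **Study Participants, Patients.** Eligibility requires reading French and being able to consent.
- **Table 1.** The primary composite comes from administrative databases. CTM-3, anxiety and caregiver burden come from phone questionnaires.

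**The concern.** The table controls who is dialled. It has no influence on who takes part. Inflating 38 to 127 contacts restores the number of completed interviews but not their representativeness, so the article claims a property that its own planning figure contradicts.

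Taking part in a post-discharge call plausibly depends on age, frailty and how the visit went, and these are plausibly linked to the outcomes. If that selection is stable, it moves the whole series up or down and leaves the before/after contrast intact. If it changes around the start of the program, the segmented regression has nothing with which to separate a change in who answers from a change in the quality of transitions. The program gives a plausible route to such a change: it adds geriatric nurses, communication tools and, for eligible patients, monthly phone check-ups, any of which might alter which seniors take the call. This is a risk and has not been shown to occur.

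**Working it through.** **1. The plan's own figure.** Rejection is 0.70, so the participation share is r = 1 − 0.70 = 0.30. Contacts needed are 38/0.30 = 126.7, rounded up to 127, which matches the article. Five calls a day for 30 days is 150 calls and 150 × 0.30 = 45 participants. Both are calculations of count only.

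**2. Bias of a monthly mean.** Let D be the mean of participants minus the mean of non-participants. The mean of everyone called is r × (participant mean) + (1 − r) × (non-participant mean), so the participant mean is off by (1 − r) × D. The article does not give D. With r = 0.30:

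| Assumed D (CTM-3 points) | Bias = 0.70 × D |
|---|---|
| 2 | 1.4 |
| 5 | 3.5 |
| 10 | 7.0 |
| 15.7 (= 11/0.70) | 11.0, the plan's difference |

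**3. What reaches the before/after contrast.**
- r and D both constant: the bias cancels from the level change and the slope change.
- r rises from 0.30 to 0.40 with D fixed at 5 to 10: the series moves by −0.10 × D, that is −0.5 to −1.0 point. If r rises to 0.50, it moves −1.0 to −2.0 points.
- D shifts by 5 points with r fixed at 0.30: the series moves by 0.70 × 5 = 3.5 points, up if D grows and down if D shrinks.

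On direction: suppose frailer seniors score lower and take part less (D above 0), and the program makes them more willing to answer. D then shrinks and the observed mean falls. That would hide a benefit. The opposite shift would mimic one.

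**4. Scale against sampling error.** Assume 12 months before and 12 after at 38 patients a month in one hospital, SD 23, a simple difference of means, and no trend or autocorrelation. The standard error is 23 × √(1/456 + 1/456) = 1.52 points. With only 3 months before (the article's minimum ahead of Phase IA) and 12 after, it is 23 × √(1/114 + 1/456) = 2.41.

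| Spurious shift (points) | False-positive rate, 12 v 12 months | False-positive rate, 3 v 12 months |
|---|---|---|
| 1 | 10% | 7% |
| 2 | 26% | 13% |
| 3.5 | 63% | 31% |

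The nominal rate is 5%. A fit with trend terms would have a larger standard error, so these rates lie towards the high end.

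**5. Price of weighting.** The Kish design effect is 1 + CV², where CV is that of the weights (assumed).

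| CV | Design effect | Effective n from 38 |
|---|---|---|
| 0.3 | 1.09 | 34.9 |
| 0.5 | 1.25 | 30.4 |
| 0.7 | 1.49 | 25.5 |

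**The case against.** The strongest reply is that this is one overclaiming adjective, and that most of what a reader might build on it is not in the article. Several stronger readings do fail:

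- **That the monthly means will be unweighted.** The article neither states nor excludes weighting. A condensed article commonly leaves this to a full protocol or analysis plan, so its silence is no fault.
- **That 70% refuse the first call.** The article speaks of call rejection and goes straight from 127 contacted to 38 obtained. It does not say whether non-answer, ineligibility or refusal at the second contact is included. The point survives either way, since those people are missing from the sample.
- **That the series will drift and produce a false benefit.** No drift is shown, constant selection cancels, and a change could equally mask a benefit.
- **That the bias is several points.** The 3.5 and 7.0 rest on assumed gaps of 5 and 10. A simulated illustration, with age 85+ and an observation-unit stay each lowering CTM-3 by 8 points and the odds of answering to 0.45, gave a bias of 1.56 at 29.8% participation. That implies a gap of 1.56/0.702 = 2.2. A stronger-selection variant implied 2.17/0.685 = 3.2. All of these inputs are assumptions.
- **That the daily list already holds the cure.** Its variables are not given. Weighting corrects only for what is recorded, and a list of everyone discharged may include people who fail the French or consent criteria. Raking about 38 people per hospital-month on several margins would be fragile.
- **That the main result is at risk.** The primary composite is administrative and does not depend on the calls.

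What the reply does not remove is the stated property itself. Random selection of whom to call does not give a representative sample when about 30% are expected to take part.

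**Conclusion.** The point holds in a limited form. The article asserts a random and representative sample, and its own 70% rejection rate in the same paragraph means that only the call list has the random property. The wording on consecutive recruitment and the second consent step in the recruitment section add to the mismatch.

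The consequence is confined to the phone-based secondary outcomes. Their monthly level describes participants. Their before/after change is distorted only if participation, or the participant/non-participant gap, changes around implementation. The size is 0.70 × gap for the level at 30% participation. For the change it is 0.5 to 1.0 point if participation moves from 30% to 40% with a gap of 5 to 10, or 3.5 points if the gap itself moves by 5. These gaps and shifts are assumptions, because the article gives no figure for either. Without monitoring of participation, a distortion of this kind could not be recognised in the series.

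**What to change.** 1. In Sample Size and Statistical Analysis, replace the claim with a random sample of patients to call, with about 30% expected participation. Limit conclusions on the phone outcomes to participants. In Patient and Caregiver Recruitment, reconcile the description of recruitment as consecutive with the random daily draw.
2. Report participation for each hospital and month, and compare enrolled with listed eligible patients in aggregate on whatever the list or the administrative data carry. Age should be available, since the calls are restricted to patients aged 65 or over; other variables are an assumption. Aggregate counts suffice, so no individual data on non-participants need reach the study.
3. As a sensitivity analysis, show the monthly phone-outcome series weighted to those margins. Use coarse categories, or a participation model fitted per hospital over the whole period, in preference to raking each month on four margins.

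**Cost.** A short wording change, retention of list counts, and one additional analysis. The article says analysis had not begun and collection was projected to run to January 2022, so on that timeline counts could still be kept. The weighted series loses some precision (design effect about 1.0 to 1.5 under assumed inputs), corrects only for recorded variables, and may be weighted partly towards people who are ineligible. As it is a sensitivity analysis, the targets of 38 and 127 need not change. If the list proves too thin for weighting, item 1 and the participation report still stand.
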